### TS and CPM Amplitude

The amplitude of TS (*A*_*TS*_) will be measured as the difference in pain intensity elicited by the thermode during the heat test stimulation (first instance the Heat Test Stimulus). We will subtract the pain level at 0 s (time the thermode reaches the target temperature) from the pain level at 120 s, so that a positive score represents an increase in pain level. The amplitude of CPM (*A*_*CPM*_) will be measured as the difference in pain level elicited by the thermode (calculated as the average of all pain scores taken throughout the 2 min test stimulation) before and after the cold water bath, and as the difference in pressure required to reach mechanical pain threshold before and after the cold water bath.

### Statistical Analyses

The sample will be characterized using descriptive statistics. The underlying assumptions of the regression model will be verified by analyzing the residuals distribution.

The main objective (identifying predictors of excitatory (TS) and inhibitory (CPM) endogenous pain mechanisms) will be achieved through the development of two predictive models (one for each mechanism). Development of a predictive model requires two steps: (1) Building and (2) Validation, which each use their own participant cohorts (see Sample Size section). Building involves a data-driven selection of the variables to be included as predictors in the model; for each variable, the beta coefficient is calculated and fitted to the model. Validation involves testing the model with data from new participants, in order to quantify the predictive capacity of the model. Validation will be conducted twice for each model: once with a healthy cohort, and once with a chronic pain cohort.

We will use a lasso regression on the discovery cohort to determine which variables will be included in the model for each mechanism. Lasso regression fits a linear model between an outcome and a set of predictors by adding a penalty term that shrinks coefficients associated to poor predictive capacity variables to 0 (i.e., Lasso automatically excludes poor predictors). This approach thus encourages simple and sparse models, and is widely used to perform variable selection in prediction contexts (103). The penalty term involves a coefficient (often denoted by lambda) that determines the amount of shrinkage to perform. This coefficient is often set so as to maximize a cross-validation estimate of the predictive capability of a model (103). Accordingly, we will select the shrinkage coefficient that minimizes the leave-one-out cross-validation estimate of the mean square prediction error. The resulting “optimal” shrinkage coefficient will be used within the lasso regression model, and the predictors and non-zero fitted parameters will be retained to constitute our predictive model.

In order to complete the validation (validation cohort), we will calculate the mean square prediction error of the predictive model for the healthy and chronic pain cohorts. If the mean square prediction error is smaller than 10%, the model will be considered to have a good predictive value. We will compare this predictive error between the two populations, to assess whether predictors are the same between healthy and patient populations.

The second objective (i.e., estimating reference TS and CPM values in healthy subjects) will use data from the 360 healthy participants (306 from the discovery cohort and the 54 from the healthy validation cohort). Participants will be separated into subgroups based on biological sex (male, female) and age (18–39, 40–59, and 60–79 years old), for a total of six subgroups. For each subgroup, a kernel estimation method will be used to obtain density curves, from which percentile reference charts will be generated (104). These analyses will be run separately for TS and CPM data.

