## Statistical Considerations

### Sample Size

It is customary in predictive analysis to use a rule of thumb to calculate the sample size, wherein the number of subjects required for a multiple regression analysis is *n* = 10–15 subjects per variable (93). However, this rule often yields fitted models with limited predictive capabilities (94–98); as such, it is recommended that two cohorts be used: a discovery cohort, and a validation cohort—which, as their names suggest, are used to build the predictive model and to validate it, respectively (99).

We calculated a sample size of 360 participants for the discovery cohort, based on the smallest expected R^2^ (0.4) and the highest expected number of predictors (24) required to obtain a shrinkage coefficient (100) of at least 0.9 (101). The discovery cohort will be representative of the overall population, such that it will be comprised of 85% (*n* = 306) of healthy participants and 15% (*n* = 54) of patients suffering from chronic pain (102). The external validation cohort will be comprised of 54 (new) participants, corresponding to 15% of the size of the discovery cohort (103). We will use two such validation cohorts (*n* = 54 for both) in order to validate our model using both healthy participants and patients suffering from chronic pain. As such, a total of 468 participants will be recruited (360 healthy participants, and 108 patients suffering from chronic pain).

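### The validation pass mark of a mean square prediction error below 10% has no stated denominator, and read as a share of outcome variance it conflicts with the R² of 0.4 used to size the study

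*Protocol article*

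**What the plan says.** In the Protocol article, Statistical Analyses, each model is tested in new participants by computing its MSPE, once in a healthy cohort and once in a chronic pain cohort. The rule is: "If the mean square prediction error is smaller than 10%, the model will be considered to have a good predictive value". The same section uses the same quantity, without a percentage or any rescaling, to choose the lasso penalty.

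Under TS and CPM Amplitude, TS is a difference between two pain ratings and heat CPM is a difference between two average pain ratings, both recorded on the 0-100 scale described under Pain Perception. CPM is also measured a second way: "and as the difference in pressure required to reach mechanical pain threshold before and after the cold water bath". No range is given for that pressure difference, and no SD is given for any outcome.

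Under Sample Size: "We calculated a sample size of 360 participants for the discovery cohort". The basis is "the smallest expected R^2^ (0.4) and the highest expected number of predictors (24"), with the size "required to obtain a shrinkage coefficient (100) of at least 0.9". For validation: "We will use two such validation cohorts (*n* = 54 for both").

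**The concern.** A percentage limit on an MSPE has a meaning only once a denominator is named. Here there are two kinds of unit and no denominator. The candidate readings do not agree with each other: on some, a model that performs as the sizing assumes is sure to miss the mark, and on others a model that predicts nothing can reach it. The most natural way to turn an MSPE into a percentage is to divide by the outcome variance, and that reading contradicts the study's own sizing value.

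What is at stake is the label given to the validated equations. The Discussion presents them as a step toward a tool that clinicians would use to orient pharmacological treatment. Whether an equation is reported as predicting well should not depend on which denominator is supplied later.

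**Working it through.** **Inputs from the Protocol article.** Smallest expected R² = 0.4, highest expected number of predictors p = 24, target shrinkage S = 0.9, discovery n = 360, and validation n = 54 per cohort (Sample Size). Pass mark 10% (Statistical Analyses). Pain scale 0 to 100 (Pain Perception). Outcome SD: not stated, so it is treated as unknown below, with an assumed range of 5 to 45 points.

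**Step 1: the plan's own figure.** n = p(1 − R²) / [R²(1 − S)] = 24 × 0.6 / (0.4 × 0.1) = 14.4 / 0.04 = 360. The stated size is reproduced and is not in dispute. It confirms that 0.4 is the value the plan works from.

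**Step 2: 10% read as a share of outcome variance.**
- MSPE / Var(Y) = 1 − R². A ratio below 0.10 therefore needs a validated R² above 0.90.
- At R² = 0.4 the ratio is 1 − 0.4 = 0.60, six times the limit. Allowing for the estimation error of a 24-predictor least-squares fit at n = 360, it is about 0.64.
- With n = 54 and the variance taken as known, the chance of passing is P(χ²₅₄ < 54 × 0.10 / 0.60) = P(χ²₅₄ < 9), about 5 × 10⁻¹³.
- With the sample variance as denominator, none of 200,000 simulated validation samples passed. The lowest ratio was 0.27.
- The 95% range of the ratio at R² = 0.4 is 0.39 to 0.84 with known variance, and 0.43 to 0.85 with sample variance. The latter corresponds to a validated R² of 0.15 to 0.57.
- Chance of passing at higher true R² (sample variance, n = 54):

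| True R² | Chance of passing |
|---|---|
| 0.80 | 0.3% |
| 0.85 | 5.5% |
| 0.90 | 50% |
| 0.92 | 80% |

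**Step 3: 10% read as a root error below 10 points on the 0-100 scale.**
- Root error = SD × √(1 − R²). At R² = 0.4 this is SD × √0.6, so a pass needs SD < 10 / √0.6 = 12.9.
- With no predictors the root error equals the SD, so a pass needs SD < 10.
- For SD between 10 and 12.9, the R² = 0.4 model passes and the model with no predictors fails. Below 10 both pass. Above 12.9 both fail. (These are expected values; samples of 54 vary around them.)
- The pressure outcome has no stated range, so 10% of its scale is undefined.

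**Step 4: other readings on the pain scale.**
- MSPE below 10 squared points: at R² = 0.4 this needs SD < √(10 / 0.6) = 4.1, below the whole assumed range.
- MSPE below 0.10 with the scale rescaled to 0-1, that is, below 1,000 squared points: at R² = 0.4 this needs SD < √(1000 / 0.6) = 40.8. A model with no predictors also passes if SD < √1000 = 31.6.

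**The case against.** The strongest reply has four parts.

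- **One reading is coherent.** A root error below 10 points is a sensible absolute-accuracy target for an equation meant to return a predicted amplitude, and it can reward skill. At R² = 0.4 it separates the model from no model for SDs of 10 to 12.9; at R² = 0.6 the window widens to 10 / √0.4 = 15.8. This stands. A reader might infer that the rule fails on every reading, but without an outcome SD the article does not support that. What remains against this reading is its dependence on an unstated SD and its silence on the pressure outcome.
- **0.4 is a floor.** The article calls it the smallest expected R², so better performance is not excluded. This stands too, but on the variance reading even a true R² of 0.8 passes only 0.3% of the time.
- **The rule only attaches a label.** A reader might infer that it decides the main objective. It does not: predictors are selected by lasso with leave-one-out tuning, the MSPE is computed and compared between cohorts whatever the cut-off, and the reference-value objective is untouched. No data are lost if the limit is restated.
- **An analysis plan could supply details.** That covers interval methods, so the absence of a confidence interval in a condensed article is not held against it. It does not rescue the printed number: a plan that named outcome variance as denominator would still have to reconcile 10% with 0.4.

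**Conclusion.** The pass mark cannot be applied as written, because the 10% has no denominator for a quantity in squared pain points or squared pressure units. If it means a share of outcome variance, it demands R² above 0.90 against a sizing value of 0.4: an expected ratio of 0.60 against 0.10, and a pass probability at n = 54 of about 5 × 10⁻¹³. If it means a root error below 10 points, the outcome turns largely on an SD that the article does not state, with cut points at 12.9 (R² = 0.4) and 10 (no predictors), and the pressure outcome is left without a rule.

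The impossibility is conditional on the variance reading, which the article does not itself state. The figures assume normally distributed errors, and, apart from the 0.64 figure, they ignore error in the fitted coefficients, which favours the plan. It would go too far to conclude that the study must fail its validation, or that the label would necessarily be unrelated to prediction. What is established is a numeric threshold that is undefined as printed and, on its most natural reading, at odds with the sample-size basis.

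**What to change.** For each outcome and each validation cohort, replace the 10% rule with validated R² = 1 − MSPE / (variance of the outcome within that validation cohort), reported with a 95% CI and with the calibration intercept and slope. Report the root error in pain points or pressure units as a description.

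Use the within-cohort variance, not the error from predicting the discovery-cohort mean. With the discovery mean as reference, a model that merely gets the cohort's mean right scores d² / (1 + d²) when that mean is shifted by d SDs. For assumed shifts this is 0.25 / 1.25 = 0.20 at 0.5 SD and 0.64 / 1.64 = 0.39 at 0.8 SD, with no skill within the chronic pain cohort.

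Set the limit for calling predictive value good before the data are seen, at a level consistent with the planned R² of 0.4. The exact limit is the sponsor's choice, made in view of the 0.15 to 0.57 sampling range of validated R² when the true value is 0.4 and n = 54.

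The cost is a change of wording in the protocol and analysis plan. The stated success criterion changes, which is the downside, and no further data are needed.

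### Comparing one fixed equation's prediction error between healthy and chronic pain cohorts measures accuracy; it cannot establish whether the predictors are the same

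*Protocol article*

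**What the plan says.** All references are to the Protocol article, Statistical Considerations.

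- **Building (Statistical Analyses).** There is one model for temporal summation and one for conditioned pain modulation. Selection is done once, on the pooled cohort: "We will use a lasso regression on the discovery cohort to determine which variables will be included in the model for each mechanism". Sample Size describes that cohort as "comprised of 85% (*n* = 306) of healthy participants and 15% (*n* = 54) of patients suffering from chronic pain".
- **Validation (Statistical Analyses).** The existing model is applied to new people: "Validation involves testing the model with data from new participants, in order to quantify the predictive capacity of the model". This is done separately in 54 healthy participants and 54 patients, and the measure is stated: "we will calculate the mean square prediction error of the predictive model for the healthy and chronic pain cohorts".
- **Inference (Statistical Analyses).** The two errors are then used for a further conclusion: "We will compare this predictive error between the two populations, to assess whether predictors are the same between healthy and patient populations".

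The section describes no variable selection by population, no interaction between pain status and predictors, and no comparison of coefficients.

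**The concern.** The same variables and the same coefficients are used in both validation cohorts by construction. Comparing the two errors therefore shows how accurately one equation performs in each group. It does not show which variables predict in each group.

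The wrong conclusion can arise in either direction. Patients may share every predictor and coefficient and still have a larger error because their ratings are noisier or their mean differs. Patients may have quite different predictors and still show the same error because their outcomes vary less. A mean difference is plausible here, since the Introduction says that temporal summation is increased and conditioned pain modulation weakened in several chronic pain conditions.

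The section states its main objective as identifying predictors, and this is the only analysis it describes for whether the predictors carry over to patients. The article fixes both the measure and the conclusion drawn from it, so this is not a detail left to an analysis plan.

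**Working it through.** **Inputs from the plan (Sample Size).** Discovery cohort 306 + 54 = 360; validation cohorts 54 and 54; smallest expected R² 0.4; 24 predictors; shrinkage at least 0.9. The counts agree: 360 + 54 + 54 = 468. The sample size is also broadly reproduced. Setting 1 − (p − 2)(1 − R²)/[(n − p − 1)R²] = 0.9 gives n − 25 = 22 × 0.6/(0.1 × 0.4) = 330, so n = 355 against 360. That figure is not in dispute. The plan attaches no number to the MSPE comparison itself.

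**Formula.** For a fixed equation with coefficients b_m, applied to a population with true coefficients b:

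MSPE = (mean shift)² + (b_m − b)′Σ(b_m − b) + residual variance,

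where Σ is the predictor covariance in that population. Only the middle term concerns the predictors, and the total does not separate the three.

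**Illustrative assumptions (not from the plan, except R²).** Healthy outcome variance 1; R² 0.4; four equal, uncorrelated predictors of unit variance, so each squared coefficient is 0.1. Healthy MSPE = 1 − 0.4 = 0.60.

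*Predictors identical, errors differ*
- Patient residual SD 1.5 times healthy: 0.60 × 1.5² = 1.35, ratio 2.25. At 1.25 times, the ratio is 1.25² = 1.56.
- Same slopes, unexplained mean shift of 0.25, 0.5, 0.75 or 1 healthy SD: 0.60 + shift² = 0.66, 0.85, 1.16 or 1.60.

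*Predictors differ, errors identical*
- Patient outcome variance 0.2, no relation to the model's predictors: 0.4 (variance of the predictions) + 0.2 = 0.60, ratio 1.
- Two of four predictors replaced, patient residual variance 0.20: 4 × 0.1 + 0.20 = 0.60, ratio 1.

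*Predictors differ, residual variance as in healthy*
- One of four replaced: 0.60 + 2 × 0.1 = 0.80, ratio 1.33.
- Two of four replaced: 0.60 + 4 × 0.1 = 1.00, ratio 1.67.

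**Precision.** The protocol names no test. Suppose a two-sided 5% F ratio with normal, mean-zero errors and 54 per cohort. The 0.975 quantile of F(54, 54) is 1.714. Power by true ratio:

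| True MSPE ratio | Power |
|---|---|
| 1.25 | 13% |
| 1.5 | 31% |
| 2.0 | 71% |
| 2.25 | 84% |

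In simulation with the same rule, one replaced predictor was flagged in 18% of runs and two in 46%. Identical predictors with the noisier patients (ratio 2.25) were flagged in 84%.

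**What calibration would show.** The slope of observed on predicted amplitude is 1 in the noisier-patients case. It is 1 with an intercept of 0.75 in the 0.75 SD shift case. It is 0 when patients are unrelated to the model's predictors, where R² against the patients' own variance is 1 − 0.60/0.2 = −2. With two of four predictors replaced it is 0.2/0.4 = 0.5. These quantities separate cases that MSPE merges.

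**The case against.** **The comparison is weak evidence, not empty.** If residual variances and means are similar, altered relations do raise patient MSPE, as the ratios of 1.33 and 1.67 show. This stands. The comparison is a non-specific screen, and the fault lies in the conclusion attached to it.

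**The scenarios are assumed.** No section supports a 1.5-fold residual SD or a patient variance one fifth of the healthy one, and the equal-error cases need exact cancellation. They show what is possible, not what is likely. The F test is likewise assumed. This stands, but the algebra does not depend on the chosen values.

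**The model might be refitted.** The Abstract mentions two validation models and multiple regression, which could hint at this. Statistical Analyses describes only applying the existing model and comparing its error.

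**Two stronger readings are tempting and not supported.**
- A reader might infer that training on 306 healthy participants and 54 patients makes worse patient error expected anyway. It does not when the relations and residual variance are the same. A simulation with that mix (24 predictors, four active, R² 0.4, patient means on the active predictors shifted 0.5 SD, ordinary least squares rather than lasso) gave MSPE 0.645 in healthy participants and 0.646 in patients. The mix matters when relations or means differ.
- A reader might infer that this result decides whether one equation is offered to both populations. No section says so. The stated criterion is an MSPE threshold, and the Discussion calls the study a first step toward a clinical tool. For usability in patients, accuracy in the patient cohort is directly relevant, and the plan reports it.

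**Conclusion.** The planned conclusion does not follow from the planned analysis. Neither equal nor unequal MSPE can establish whether the predictors are the same in the two populations. This is a matter of logic and rests on no assumed number.

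The sizes are illustrative: a ratio of 2.25 with identical predictors, and a ratio of 1 with unrelated ones. The 1.71 cut-off and 31% power at a true ratio of 1.5 hold only for a two-sided F ratio with normal errors. On that basis, finding no difference would say little even about accuracy.

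The point should be fixed before analysis, but its reach is limited. Model building, the cohort-specific MSPE, the sample size and the reference charts do not depend on the sentence.

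**What to change.** 1. Reword the sentence so that the MSPE comparison describes predictive accuracy, or transportability of the equation, in each population and nothing more.
2. In each validation cohort, regress observed on predicted amplitude. Report the calibration intercept and slope, and R² relative to that cohort's own variance, with 95% CIs.
3. If the question of common predictors is kept, estimate pain-status-by-predictor interactions across the candidate predictors, not only those the lasso selected. Otherwise, state that variables dropped by a lasso on an 85% healthy cohort are not assessed.
4. Label step 3 exploratory. State that 108 patients give imprecise interaction estimates, and that intervals reusing the discovery data are post-selection and so too narrow at face value.

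**Cost.** Steps 1 and 2 need a few lines of text and modest analysis. Step 3 needs more work and may remain inconclusive. No new participants or measurements are needed.

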## Discussion

To our knowledge, this is the first protocol that single handedly studies psychological, physiological and socio-demographic markers of endogenous pain modulation mechanisms.

The protocol we adopted to assess TS and CPM is frequently used in our laboratory; its reliability has been validated (10–12), and our expertise with the procedure and our familiarity with the equipment considerably reduces the risk of bias and confounding factors.

Chronic pain is a highly prevalent condition, for which there is currently no satisfying treatment approach. The success rates of surgery are subpar (105, 106); therapeutic exercises (107) only have limited success; and the current pharmacological approach, which relies mostly on drawn-out trial and error, is disheartening for both the patients, who struggle to see a finality to their pain, and the clinicians, who are confronted with their powerlessness in the face of their patients' everlasting ailment (108).

It is becoming more and more apparent that chronic pain treatment should focus not on the symptomatology—or type of condition—of chronic pain patients, but rather on the underlying imbalance in their pain modulation mechanisms. The amplitude of CPM and TS has been shown to correlate with the development of chronic pain conditions (109, 110), which imparts them with a predictive quality that could be extremely useful in clinical practice. Moreover, specific assessments of CPM and TS can effectively predict treatment success rates in patients suffering from chronic pain (27). As such, an individualized pharmacological treatment informed by the pain modulation profile of each patient could significantly improve treatment outcome. Unfortunately, current CPM and TS testing procedures remain too expensive and time-consuming to be used on a regular basis in hospitals or family medicine clinics.

This study will further our understanding of modulatory mechanisms and their relationship with a complex system of physiological, psychological and socio-demographic correlates, which will allow us to develop a predictive model to compute the pain modulation profile of individual patients based on their biopsychosocial characteristics. This model will consist in a simple equation in which clinicians can input the value of selected variables (obtained via simple clinical tests), in order to yield the predictive amplitude of their patients' CPM and/or TS response. The overarching goal of this study is to provide clinicians with a set of quick and cheap tests, easily applicable in day-to-day practice, in order to identify markers of pain modulation profiles and in turn orient pharmacological treatment, which will ultimately provide patients with a more hopeful outlook on their future and will lead to a more optimal use of ever limited health care resources. This protocol is the first step toward the development of a validated clinical tool.

